### Primary outcome measures

Measures of psychopathology, symptoms of depression and symptoms of anxiety are used as a composite primary outcome measure [34]. This composite measure consists of the Brief Symptom Inventory [35], the Beck Depression Inventory II [36] and the Beck Anxiety Inventory [37].

#### Brief symptom inventory

The Brief Symptom Inventory (BSI; [35]) is a self-report measure consisting of 53 items and detecting the subjective impairment by a range of psychological symptoms during the last seven days. The BSI offers information about the psychological burden with regard to nine subscales: somatization, obsessive-compulsive, interpersonal sensitivity, depression, anxiety, hostility, phobic anxiety, paranoid ideation, psychoticism. As an economic screening instrument with robust psychometric properties, this inventory is commonly administered to detect pre-post changes [35].

#### Beck depression inventory II

The revised version of the Beck Depression Inventory (BDI-II; [36]) is a self-assessment tool consisting of 21 items to determine depressive symptoms during the past 2 weeks. The BDI-II is not only an indicator of the severity of depressive symptoms in accordance with DSM-IV but also one of the most widely used self-report measures for depression in clinical practice and research [38]. It has shown robust psychometric properties [36].

#### Beck anxiety inventory

The Beck Anxiety Inventory (BAI; [37]) is a self-report questionnaire to detect the severity of anxiety symptoms. The BAI consists of 21 descriptive statements with regard to symptom severity during the last 7 days. 13 of 21 items detect physiological symptoms, five items measure cognitive aspects of anxiety and three items refer to both, somatic and cognitive symptoms. The BAI can be cited as a reliable and valid questionnaire [37].

### Secondary outcome measures

#### World Health Organization

The WHO-5 [39] is a short questionnaire measuring subjective psychological wellbeing over the past 2 weeks using five items. A low value indicates low wellbeing and quality of life and a high value is associated with wellbeing and high quality of living. The WHO-5 has shown to be a sensitive and specific screening instrument for depression [40]. The clinimetric validity, the responsiveness and sensitivity were evaluated. The WHO-5 performed well with regard to all these aspects [40].

#### Short Form of the Health Survey

Health-related quality of life is measured with the Short Form of the Health Survey (SF-12; [41]). Its two subscales measure physical and mental aspects of health-related quality of life. It captures general health as well as pain, disabilities in daily life and mental problems. The SF-12 asks for the presence and severity of 12 items over the course of the last 4 weeks. The re-test reliability is good and roughly equivalent to the long form [42].

#### Emotional competence

Emotional Competence is measured by the SEK-27 [43]. The emotional competence is recorded both, in general (trait) as well as with respect to the last week (prolonged state). The questionnaire consists of 27 items that are resumed to nine subscales: attention, clarity, body perception, understanding, acceptance, resilience, self-support, willingness to confront and regulation. The total value generally corresponds to the constructive handling of negative emotions. The SEK-27 is a reliable, valid and sensitive self-assessment measure for the constructive dealing with negative emotions [43].

#### Inventory of interpersonal problems

The Inventory of Interpersonal Problems (IIP-32; [44]) is a questionnaire for the self-assessment of interpersonal problems. With the help of this instrument patients can describe how much they suffer from specific difficulties in dealing with other people. The IIP-32 consists of 32 items and the eight scales correspond to the octants of the Interpersonal Circle [45]: too autocratic/dominant, too expressive/intrusive, too caring/friendly, too exploitable/resilient, too insecure/obsequious, too introverted/socially avoidant, too repellent/cold, too quarrelsome/competitive. In addition, a total value is formed which characterizes the degree of interpersonal problems. The IIP-32 has shown adequate psychometric properties [46].

#### Inventory of approach and avoidance motives

The Inventory of Approach and Avoidance Motives (IAAM/German: FAMOS; [47]) assesses motivational goals of psychotherapy patients. The FAMOS consists of 94 items, which are rated in terms of their importance. The motivational goals are differentiated into approach-goals (14 scales; intimacy, socializing, helping others, recognition, impressing, autonomy, performance, control, education, faith, variety, self-confidence, self-rewarding) and avoidance-goals (nine scales; loneliness, contempt, humiliation, criticism, dependence, tension with others, being vulnerable, helplessness, failure). The FAMOS is both, a diagnostic tool in the context of treatment planning as well as a measure of change throughout psychotherapy and has shown good psychometric properties [47].

#### Incongruence questionnaire short version

The Incongruence Questionnaire Short Version (K-INK; [48]) is a procedure for the determination of incongruities between the perceived reality and the motivational goals of psychotherapy patients. The K-INK is based on the Inventory of Approach and Avoidance Motives [47] and the consistency theory by Grawe [5]. The short version of the INK includes the 23 items of the long version with the highest item-total correlation with each of the 23 INK-scales, whereby 14 target the approach-goals and nine items target the avoidance-goals. The INK is the second questionnaire to attempt the building of a test-theoretical basis for Grawes psychotherapy research approach and has shown good psychometric properties [48].

### Clinician administered measures

#### Structured clinical interview for DSM-IV

The patients’ diagnostic status at baseline will be assessed with an interview of about one and a half hours conducted by trained raters (therapists in training) using the Structured Clinical Interview for DSM-IV (SCID; [49]).

#### Hamilton depression rating scale

The Hamilton Depression Rating Scale (HAMD; [50]) is administered together with the SCID. It is a well-established clinician-rated assessment of depressive symptom severity and encompasses psychological and somatic symptoms. The clinician rates the severity of these symptoms based on patient reports and his or her own observation.

#### Goal attainment scaling

The Goal Attainment Scaling (GAS; [51]) is a tool for the definition of individual goals and the evaluation of goal attainment in psychotherapy. The patient can indicate to what extend he/she was able reach the individual goals that were formulated at the beginning of psychotherapy on a 7-point scale from -2 to 4. Point 0 describes the current state of the problem, point +4 describes the desirable state and -2 the state if the problem deteriorated. The GAS interview is conducted with the patient by trained Master students.

### Process measures

#### Bern post-session report

The Bern Post-Session Report (Patient and Therapist Version; BPSR-P/BPSR-T; [52]) is an instrument for the assessment of treatment processes and a regular quality-monitoring tool, completed at the end of each therapy session. The patient version consists of 32 bipolar items which are rated on a scale ranging from -3 = not at all to +3 = yes exactly. The subscales include resource activation, positive bonding experiences, positive therapeutic relationship, problem mastery, positive problem solving experience, positive clarification experiences and treatment progress.

The therapist version assesses the treatment processes from the therapists’ perspective and consists of 27 bipolar items, which are also rated at the end of each therapy session. The subscales include resource activation, therapeutic relationship, openness and engagement, willingness to work hard, problem mastery, problem solving, motivational clarification, treatment progress, interactional perspective and interactional difficult. Further, new items concerning the study-specific interventions were added to the Bern Post-Session Report Therapist Version (see Table 4).

**Table 4 Tab4:** Checklist of the study-specific interventions implemented in the therapy session

Today I conducted emotion-focused intervention(s)	
If so, which emotion-focused interventions (empathic exploration, empathic validation, engendering of a medium degree of emotional activation, focusing, allowing and expressing emotions, biographical work, systematic evocative deduction, two-chair dialogue, empty-chair dialogue, other Emotion-focused intervention)?	
Today I conducted intervention(s) to improve self-regulation (SR)	
If so, which interventions fostering self-regulation (explanation of the SR-model, clarification, deliberate reflection of goals and values, derivation of ideals and norms from personal history, attention-regulation, work on self-instruction, regulation of behavior, regulation of the body, emotion-regulation, other self-regulatory interventions)?	
Has it been difficult to integrate emotion-focused components into today’s therapy?	
If so, which difficulties occurred?	
Has it been difficult to integrate self-regulation into today’s therapy?	
If so, which difficulties occurred?	
Did you have reasons to not realize any study-specific interventions?	
If so, which reasons would that be?	

#### Symptom check list

The Symptom Checklist - 9 (SCL-K-9; [53]) is a short form of the revised Symptom Checklist (SCL-90), which in turn is a previous version of the Brief Symptom Inventory. The results of the SCL-K-9 on session-level thus correspond to the results of the BSI total score (General Symptom Index; GSI) as a primary outcome measure (measured at pre, post and follow-up). The SCL-K-9 assesses the construct of psychological distress through symptom severity. The SCL-K-9 is composed of nine items corresponding to the nine scales of BSI and SCL (see above). It is a reliable and valid instrument that is used in clinical diagnostic and in practice as a measure of quality assurance [54].

#### Classification of affective meaning states

The Classification of Affective Meaning States (CAMS; [55]) is a process rating system for the systematic identification, observation and measurement of distinct emotional states in psychotherapy sessions. This observer-based rating system was developed based on emotion-focused theory [9]. The CAMS assesses ten affective meaning states that can be ordered on nine different levels of emotional transformation referring to a sequential model of emotional processing [21]. In several studies an excellent inter-rater reliability was reported [56].

#### Experiencing scale

The Experiencing Scale (EXP; [57]) is a rating scale assessing the degree to which clients orient to, symbolize, and use internally felt experiences as a source of information when solving their problems. Raters use verbal communication, including features of content, expression, grammatical selection and paralinguistic to code segments of therapy. Ratings on the lower scale levels represent clients’ attempts to identify and symbolize their internal experience. Higher scale levels by contrast reflect the clients’ efforts to use an experientially- oriented understanding for problem solving. The Experiencing Scale stands among the most studied and validated observational measures in psychotherapy research [57].

Depth of change will be measured by the observer-rated CAMS and EXP as well as by patient and therapist rated process questionnaires (e.g. problem actuation, clarification, emotional processing, and experiencing).

### Procedure

Patients are randomly assigned to the TAU + EFT or TAU condition. The patients receive 25 ± 3 sessions of weekly Psychological Therapy with or without integration of EFT elements. Both groups are assessed at baseline (t0), immediately after completing therapy (t3, 25 sessions), for intermediate measurements (t1, 8 sessions; t2, 16 sessions) and at 6, 12 and 36 month follow-up (t4, t5, t6) with an elaborated measuring battery (see Table 2). Additionally, participants and therapists complete self-report measures after every session for the detection of the treatment process and symptom severity. All data will be saved in an anonymous way only identified by a code, which is not related to the participant’s identity. Servers are protected by high-end firewall systems. Only the researchers directly involved in the study have access to the data. The procedure is shown in Fig. 2.

**Fig. 2 Fig2:**
[figure not shown]
Procedure of the study

### Analysis

Baseline descriptive statistics will be generated for all randomized patients and compared between the two study arms with ANOVA (for continuous variables) and χ2 statistics (for categorical variables). Missing values will be substituted with the procedure of multiple imputation. The research questions will be examined with the appropriate multilevel approaches, mainly two-level regression and growth analyses. These approaches take into account non-independence of observations in repeated measures outcome and the different number of sessions attended by the patients. Furthermore, we intent to test potential variability within therapists based on a longitudinal three-level model. The primary outcome analysis will be a modified intention-to-treat analysis that includes all patients who were randomized and attended at least one therapy session. These analyses will compare treatment differences in continuous outcome variables over time for TAU + EFT and TAU. Separate multilevel analyses will be run for the primary and each of the secondary outcome variables across three time points (pretreatment, post- treatment, 12-month follow-up). We expect primary and secondary outcome measures to be highly inter-correlated loading on one outcome factor [34]. For the purposes of the present study, a standardized composite measure taking primary and secondary symptom-related, self-report measures into account will be reported. Models will be run assuming random intercepts and slopes. For the main research questions, level-one models of individual change over time and level 2 models for the between-subjects factors are conducted. Each analysis will examine the overall effect of change over time (time), the difference between TAU + EFT and TAU, and the differences in changes over time by condition as a cross level interaction. To assess maintenance of gains, the multilevel regression analyses will be repeated with just the post-treatment and follow-up time points. A secondary series of analyses will include only those patients who completed the originally allocated treatment. Mechanisms of change will be examined as mediation effects in multilevel regression and structural equation models. Moderator effects will be analyzed as cross level interactions. Therapist effects will be investigated in three-level models. Multiple regression models will be used to predict residual change in the composite score between post and follow-up, by the level of structural change at post-treatment.

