Nevertheless, it is uncommon to study such integration, and research on its effects on process and outcome is rather rare [16]. Thus, more research on psychotherapy integration is needed, if psychotherapy research is to cover real practice in an endeavor to reduce the currently much bemoaned scientist-practitioner gap. The main aim of this study is to compare Psychological Therapy corresponding to the usual practice in Bern to Psychological Therapy with integrated EFT elements. A central characteristic of the presented project is its external validity being particularly evident in the elaboration of naturalistic conditions and treatment as usual (TAU) being part of both conditions (TAU + EFT and TAU). Twenty-three therapists per condition treat a total of 130 patients from the outpatient clinic of the University of Bern, suffering from depressive, anxiety and adjustment disorders. Therapists vary in their general therapy experience and extent of training. This will allow for evaluating the influence of these variables. To secure balance regarding the amount of training and supervision between the project conditions, TAU without EFT will be supplemented with additional units elaborating on some elements that are already part of PT.

The overarching question addressed is: What are the consequences of systematically integrating emotion-focused concepts and interventions into Psychological Therapy? This is seen as exemplary for major steps in therapy development in the sense of General Psychotherapy and follows suggestions by others [19]. The general research question can be subdivided into the following questions:Is there a general superiority of TAU + EFT over TAU in the changes from pre to follow-up (with indicators such as stability of change, post-therapeutic gain, and reduction of relapses)?Is there a superiority of TAU + EFT over TAU in variables indicating deeper levels of processing?Are there negative side effects of the integration e.g. due to less attention and time dedicated to more traditional but useful elements and procedures?Additional exploratory research questions include the examination of potential predictors, moderators and mediators of outcome (e.g. symptom severity, onset of primary disorder, previous psychotherapies, and process variables such as experiencing ratings).

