### Sample size calculation

Based on a power analysis with G*Power [25] an optimal total sample size of 130 patients allows for the detection of a small effect (Cohen’s f = 0.10) for the interaction between time (pre, post, follow-up) and treatment condition (TAU + EFT vs. TAU) (repeated measures analyses of variance (ANOVA), within-between-interaction; *α* = 0.05; power = 0.80; number of groups = 2; number of measurements = 3; pre-post correlation of pre-post values: *r* = 0.6; non-sphericity correction = 1). Multilevel models allow for assessment-by-assessment approaches: Assuming 130 patients and three assessments per patient (pre, post, follow-up), the resulting N would be 390. Further assuming a 20% dropout rate at follow-up, this sample would be reduced to 312. This would enable the detection of small effects of 3.4% explained variance in a regression model (linear multiple regression: random model; H1: ρ2 > 0; α = 0.05; power = 0.80) with three predictors (treatment condition, time, and their interaction); and would still allow the identification of small effects of 5.1% explained variance in a model including additional covariates with a total of ten predictors [25].

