A methodologically fundamental question is how therapist variance shall be controlled. It may seem like an ideal solution to let the same therapists conduct therapies in both conditions, and some studies actually use this strategy [22, 58]. However, having the same therapists in both conditions does not necessarily ensure that their preferences, belief in the methods, fit of the personal profile with the method, competencies etc. are equal between the two conditions, but may vary between the two conditions within one and the same therapist. In addition, it has been argued plausibly that there may be considerable carry-over effects when using therapists in more than one condition [63]. Whereas both options seem viable, we decided in this trial to control at the level of relevant psychological variables. Therapist variables (e.g., therapist experience in the respective condition) will be assessed, and their impact on differential change in the outcome variables will be investigated and taken into account in the interpretation of potential differences between the groups. We will also be able to test for differential effects, e.g. whether good effects depend on therapist experience in one but not the other condition. Also higher order interactions can be studied, e.g. whether the readiness of a particular kind of patient to engage in particular interventions depends on the perceived therapist competence, etc.

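### The model for the treatment comparison has no therapist level although therapists are nested in arm; if therapists differ in their patients' change, the nominal 5% test is somewhat anti-conservative

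*Protocol article*

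**What the plan says.** **Therapists belong to one arm.** The Background states: "Twenty-three therapists per condition treat a total of 130 patients from the outpatient clinic of the University of Bern". The Discussion considers letting the same therapists work in both conditions, mentions carry-over as an argument against it, and settles on another route: "we decided in this trial to control at the level of relevant psychological variables". Therapist variables are to be measured, and their impact considered when group differences are interpreted.

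**The treatment comparison has two levels.** The Analysis section says: "For the main research questions, level-one models of individual change over time and level 2 models for the between-subjects factors are conducted". The difference in change between conditions is tested as a cross-level interaction. The dependence that these models are said to handle is that of repeated measures; differing numbers of sessions are also mentioned, but shared therapists are not.

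**The therapist level appears separately.** "Therapist effects will be investigated in three-level models". A longitudinal three-level model is also announced, to test variability connected with therapists. Neither sentence makes a three-level model the basis for the arm contrast.

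**The sample size** of 130 "allows for the detection of a small effect (Cohen’s f = 0.10) for the interaction between time (pre, post, follow-up) and treatment condition". No therapist ICC or design effect enters the calculation.

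**The concern.** Because a therapist delivers only one condition, condition varies between therapists and not within them. Any real spread between therapists in their patients' improvement then adds to the variance of the difference between arms. A model with patients as its top level treats the 65 patients in an arm as independent and does not count that spread. A chance difference between two groups of 23 therapists can then be read as an effect of integrating emotion-focused components.

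This bears directly on the trial's aim. The intervention reaches patients through therapist training and supervision, and the Discussion hopes to conclude whether an 8-day training plus supervision makes usual treatment more effective. That conclusion generalises over therapists. The Participants section deliberately mixes 5 experienced therapists with 18 in training per condition, so some variation between therapists is plausible.

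Measuring therapist variables and weighing them in interpretation does not change a standard error, and measured characteristics do not absorb the unmeasured part of therapist variation.

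**Working it through.** **1. The plan's own figure.** Inputs from Sample size calculation: f = 0.10, "within-between-interaction; *α* = 0.05", "power = 0.80; number of groups = 2; number of measurements = 3", "pre-post correlation of pre-post values: *r* = 0.6; non-sphericity correction = 1", N = 130.

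- Noncentrality: λ = f² × N × 3 / (1 − r) = 0.01 × 130 × 3 / 0.4 = 9.75
- Degrees of freedom: (2 − 1)(3 − 1) = 2 and (130 − 2)(3 − 1) = 256
- Power: 0.8001 at N = 130 and 0.793 at N = 128

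The stated 130 is reproduced exactly, with all patients treated as independent.

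**2. Cluster size.** 65 / 23 = 2.83 patients per therapist; 46 therapists in all; 46 − 2 = 44 degrees of freedom for a contrast between therapists.

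**3. ICC.** The protocol gives none, so a range is assumed. For the time-by-condition effect, the ICC that matters is that of change. A stable therapist effect on outcome level cancels in a change contrast.

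**4. Formulas.**

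- Design effect: DE = 1 + (65/23 − 1) × ICC = 1 + 1.826 × ICC
- Actual type I error of a nominal 5% test: 2 × [1 − Φ(1.96 / √DE)]
- Power with clustering: step 1 with λ = 9.75 / DE

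| Assumed ICC on change | DE | Standard error too small by | 1.96/√DE | Type I error | λ | Power at N = 130 |
|---|---|---|---|---|---|---|
| 0 | 1.000 | 0% | 1.960 | 5.0% | 9.75 | 80% |
| 0.02 | 1.037 | 1.8% | 1.925 | 5.4% | 9.41 | 78.5% |
| 0.05 | 1.091 | 4.3% | 1.876 | 6.1% | 8.93 | 76% |
| 0.10 | 1.183 | 8.0% | 1.802 | 7.2% | 8.24 | 73% |

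The power column keeps the plan's 256 denominator degrees of freedom and full follow-up. Therapist-based degrees of freedom or dropout would lower it further.

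**5. Simulation.** With 100,000 simulated trials per setting and near-equal caseloads (19 therapists with 3 patients and 4 with 2, per arm), a test on patient change scores that ignores therapists rejected in 5.6%, 6.1% and 7.1% at ICC 0.02, 0.05 and 0.10. A test on therapist means stayed between 4.9% and 5.1%.

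**6. Uneven caseloads.** The protocol gives only an average caseload. If the coefficient of variation were 0.6 (an assumption for illustration), DE = 1 + [(1 + 0.6²) × 2.83 − 1] × ICC. The type I error is then 5.7%, 6.7% and 8.4% at ICC 0.02, 0.05 and 0.10.

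**The case against.** **Therapists are not ignored.** Three-level models are planned, two-level models are only the main approach, experience is balanced by design (5 and 18 per arm), and training and supervision are equivalent. A reader might infer that the protocol overlooks therapists altogether; it does not. But balance in experience leaves random therapist variation in place, and the three-level models have another stated purpose. What stands is narrower: the therapist level is absent from the model named for the main questions.

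**The inflation is conditional and small.** A reader might infer that the standard errors are too small as a matter of fact. The protocol gives no ICC, and if therapists do not differ in their patients' change the two-level test keeps its 5%. With fewer than three patients per therapist, the excess is about 0.4 to 2 percentage points over the assumed range of 0.02 to 0.10. Larger figures need caseload patterns that the protocol does not state. This objection stands and sets the weight of the point.

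**The power loss is not caused by the choice of model.** This also stands. It follows from nesting therapists in arm, and a correct model reveals it without repairing it.

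**A three-level fit may collapse.** In a one-way approximation with 44 and 84 degrees of freedom, the estimated therapist variance is zero or below in about 43%, 31% and 16% of trials at ICC 0.02, 0.05 and 0.10, and the fit then largely returns to two levels. This is a reason to fix the therapist-level degrees of freedom beforehand so that they do not depend on the estimate. It is not a reason to omit the level.

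**Conclusion.** The point holds in a limited form. Separate therapists per arm and a two-level treatment model are both on the page, and no therapist clustering enters the stated arm comparison. If therapists differ in their patients' change, the time-by-condition test is anti-conservative: about 5.4% to 7.2% in place of 5% for an assumed ICC on change of 0.02 to 0.10, and somewhat more with uneven caseloads. At ICC 0 there is no excess. These figures assume about 2.83 patients per therapist and complete data.

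The documents do not support saying that the error rate does exceed 5%, or by how much. The plan should be corrected on this point, because the error can only run towards intervals that are too narrow, it affects the primary comparison, and the better model is already planned. The size does not make it a fatal defect.

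**What to change.** **Analysis.** Name the three-level model (assessments within patients within therapists) as primary for condition and time-by-condition. Include a therapist random intercept and a therapist random time effect, simplified only if the model does not converge. Fix small-sample degrees of freedom based on about 44 at the therapist level in advance, so that the reference distribution remains therapist-based even when the estimated variance is near zero. Report the two-level model as a sensitivity analysis.

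Adding therapist experience as a covariate may be useful in its own right, but it does not correct the standard error and is no substitute.

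**Sample size calculation.** State that 80% power at 130 patients assumes no therapist clustering, and give the range: about 78.5%, 76% and 73% at ICC 0.02, 0.05 and 0.10, before dropout. Restoring 80% would take about 136, 142 or 154 patients on the same assumptions. The change of model does not do this.

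**Cost.** A change of wording around a model already intended, slightly wider confidence intervals, and a less favourable stated power. At the reported trial status 28 patients had been recruited, so the choice could still be fixed well before the final comparison.
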